### Adverse events and serious adverse events

Possible adverse events of bronchoalveolar lavage include anesthesia accidents, bronchospasm, pneumothorax or mediastinal emphysema, exacerbation of hypoxia, and respiratory or cardiac arrest. Record whether each subject undergoing bronchoalveolar lavage experiences adverse events and what specific adverse events occur. Serious adverse events are defined as respiratory or cardiac arrest or any adverse event that leads to the termination of bronchoalveolar lavage procedure.

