## Introduction

### Background

Severe pneumonia caused by various pathogenic microorganisms is a leading cause of hospitalization and death worldwide [1]. The inappropriate application of antibiotics for pneumonia at early stages is the major reason for the increased morbidity and mortality rates [2]. If treatment is delayed, severe pneumonia can progress to multiple organ dysfunction and even death. Despite significant advances in etiological research and antimicrobial treatment, severe pneumonia remains the leading cause of death from infectious diseases worldwide [3]. In addition to the necessary mechanical ventilation, early, rapid, and accurate pathogen diagnosis can help clinicians select targeted treatment options, thus improving prognosis and reducing mortality rates [4].

Traditional microbiological tests include smear, culture, serology, and limited molecular panels. These methods are unable to identify the full range of potential pathogens (e.g., fastidious or nonculturable organisms or uncommon organisms not included in current panels). In addition, in many clinical laboratories, culture is very time consuming, requiring a 3–5-day wait time to get an accurate report. Serological testing and PCR require a priori assumption about the presence of a particular virus and require the laboratory to have the appropriate commercial kit. These conditions often lead to missed detection of certain pathogens [5]. Previous studies have shown that metagenomic next-generation sequencing (mNGS) has a higher sensitivity and broader pathogen spectrum than traditional microbiological tests. Recently, the possibility of using mNGS to identify non-sterile site specimens in the respiratory tract has been discussed. mNGS is assumed to optimize antibiotic treatment in critically ill patients with infectious diseases. While helpful, little is known about how to interpret the application of mNGS results in lower respiratory tract infections (LRTIs), which leads to conflicting opinions, as mNGS does not elucidate whether the organism is viable or a pathogen. Incorrect interpretation or false positive results perhaps escalate antimicrobial regimen [6]. This may result in inappropriate treatment, which may prolong or aggravate the status of disease. In particular, prospective clinical trial and economic data showing the cost-effectiveness of these relatively expensive tests in improving patient outcomes are needed to justify their use.

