### Intervention

For both groups, bronchoalveolar lavage fluid will be harvested within 24 h of participants entering the ICU. Traditional microbiological tests will be collected as soon as possible after admission and will be performed in local in-house laboratories. Traditional microbiological tests, including culture, antigen detection, multiplex PCR, and direct microscopic examination of specimens. The results of traditional microbiological tests will be interpreted according to standard procedures.

BALF specimens will be divided into aliquots and used for both mNGS tests and traditional microbiological tests for study group. BALF mNGS tests will be transferred to the same professional genomic laboratory independently by cold chain transportation. The genomic laboratory will perform nucleic acid extraction, library construction, amplification and sequencing, bioinformatic analysis, and data interpretation according to previous clinical practice.

In the study group, anti-infective treatment regimen is based on both BALF mNGS and traditional microbiological tests, while in the control group, it is based on the results of traditional microbiological tests. The results of mNGS and necessary clinical data will be judged by a group of senior clinicians, who reached a unified opinion.

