## Discussion

Over the years, traditional microbiological methods for pulmonary infective diseases include a variety of culture-based approaches, visualization by microscopy, antigen detection, serological methods, and molecular detection. Recently, metagenomic NGS has become a well-established method in clinical microbiology laboratories to aid in the diagnosis of infectious diseases. Next-generation sequencing was originally used for applications such as oncology and inherited disease diagnosis. Targeted traditional microbiological methods detect a defined spectrum of organisms. By contrast, untargeted mNGS offers the unique advantage of broadly identifying organisms, particularly those are fastidious or non-culturable or rapid diagnostics unavailable [6, 10]. Furthermore, mNGS has demonstrated improved detection of mixed pulmonary infections in relation to traditional microbiological tests [11].

The clinical benefits of mNGS are potentially significant, but its limitations should also be considered. A significant potential limitation of mNGS assays for infectious disease diagnostics is the possibility of false-positive results due to contamination. Contamination of respiratory specimens by normal microbiota during the process of collection is highly likely, as the respiratory tract is not a sterile system [12]. Thus, quality control for mNGS assays is critical to ensure accurate performance. In our study, the establishment and monitoring of robust mNGS quality control metrics have been successfully adapted to the clinical microbiology laboratory setting despite of complex multistep tests. Moreover, considered as sterile respiratory specimen, BALF will be collected in this study.

Another potential limitation of mNGS assays for infectious disease diagnostics is that mNGS provides valuable information regarding the presence of genetic material but does not elucidate whether the organism is viable or a pathogen [12]. The interpretation and reporting of mNGS data from a respiratory sample are complex. Interpreting organisms without clear clinical presentation, patient history and risk factors, and results from traditional microbiological tests could lead to misdiagnosis and inappropriate treatment, negatively impacting patient care [13]. In this study, we will evaluate clinical effectiveness and risks of mNGS based on traditional microbiological tests, namely primary and secondary outcomes.

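### Seriousness of adverse events is tied to arrest or to ending the lavage, so a life-threatening complication found after a completed lavage is recorded but graded non-serious, and reactions to test-guided anti-infective treatment are not named

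*Protocol article*

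**What the plan says.** The Protocol article, section Adverse events and serious adverse events, has three sentences.

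- It lists what may happen: "Possible adverse events of bronchoalveolar lavage include anesthesia accidents, bronchospasm, pneumothorax or mediastinal emphysema, exacerbation of hypoxia, and respiratory or cardiac arrest".
- It sets the recording rule: "Record whether each subject undergoing bronchoalveolar lavage experiences adverse events and what specific adverse events occur".
- It defines seriousness: "Serious adverse events are defined as respiratory or cardiac arrest or any adverse event that leads to the termination of bronchoalveolar lavage procedure".

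The Intervention section says who has the procedure: "For both groups, bronchoalveolar lavage fluid will be harvested within 24 h of participants entering the ICU". It also says what separates the arms: "In the study group, anti-infective treatment regimen is based on both BALF mNGS and traditional microbiological tests", whereas control patients are treated on traditional results alone.

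The Background names a possible harm of the added test: "Incorrect interpretation or false positive results perhaps escalate antimicrobial regimen". The Discussion says where that harm will be looked for: "we will evaluate clinical effectiveness and risks of mNGS based on traditional microbiological tests, namely primary and secondary outcomes".

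**The concern.** A seriousness grade should tell the reader how badly the patient was affected. Here, apart from arrest, it depends on whether the operator ended the procedure. Two patients with the same complication and the same consequence can be graded differently because of when it was noticed.

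The second part is coverage. The randomised contrast is the information that guides anti-infective treatment. A patient in either arm can have a drug reaction, and its frequency could differ by arm if mNGS changes what is prescribed. The adverse-event section does not mention such reactions, although the article itself raises inappropriate treatment as a risk of mNGS.

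At stake are the accuracy of the serious-event tally and the completeness of the evidence on the risks of mNGS. The primary comparison of mortality is not affected.

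**Working it through.** The point rests on no figure in the plan, so the check is to apply the stated rule to cases and then compare it with the outcome list.

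**Step 1. Apply the definition.** There are two criteria: (a) respiratory or cardiac arrest; (b) any adverse event that ends the lavage.

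| Case | Recorded as adverse event? | (a) | (b) | Grade |
|---|---|---|---|---|
| Life-threatening pneumothorax found after a completed lavage, no arrest | Yes, a listed event | No | No | Non-serious |
| Life-threatening worsening of hypoxia after a completed lavage, no arrest | Yes, a listed event | No | No | Non-serious |
| Bronchospasm that ends the lavage and then resolves | Yes, a listed event | No | Yes | Serious |
| Arrest some time after the lavage | Yes, a listed event | Yes, no time limit is stated | No | Serious |
| Severe non-fatal reaction to an anti-infective drug after the lavage, no arrest | Not named; only on a broad reading of the recording rule | No | No | Non-serious |

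Rows 1 to 3 show the misclassification: the events with the graver consequence receive the lower grade. In the last row, even the broad reading does not rescue the grade, because a reaction that arises after the procedure is over cannot end it.

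**Step 2. Does the section address what differs between arms?** Both arms have lavage. The specimen must be taken before it can be sequenced, so a complication of taking it cannot result from an mNGS report. A tally of lavage complications therefore describes the safety of the procedure, not of the randomised strategy.

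**Step 3. Do the outcomes fill the gap?** The Discussion assigns the risks of mNGS to the primary and secondary outcomes. From the Outcomes section:

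| Type of harm | Outcome that bears on it |
|---|---|
| Death | Primary outcome, all causes to day 28 |
| Longer illness | ICU and hospital stay; days out of ICU |
| Organ support | Ventilator-free days; vasopressor duration |
| Antimicrobial exposure | Types and duration of regimens |
| Resistance | Source of drug-resistant organisms |
| Adverse reaction to an anti-infective drug | None |

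Regimen type and duration measure exposure, not harm. Stay and organ support respond to drug toxicity, but they cannot separate it from the pneumonia.

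**Step 4. Scale of the background event rate.** This bears on how the fix is drafted. The Sample size section assumes 28-day mortality of 15% and 33%. With 192/2 = 96 per arm, expected deaths are 96 × 0.15 = 14.4 and 96 × 0.33 = 31.7, about 46 in total. An outcome-based definition without an attribution limit would sweep in most of these as disease events already counted as the primary outcome.

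**The case against.** The strongest reply is that the article does say where mNGS risk is assessed. The sentence in the Discussion points to the primary and secondary outcomes, and these cover the named pathway of escalation and prolonged illness quite well. This stands, and it rules out several stronger readings that a reader might infer.

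- *Only lavage harms are recorded, and later serious events are missed.* Not supported. Deaths, stay, organ support, antimicrobial exposure and resistance are outcomes, a late pneumothorax is still recorded, and a late arrest is not excluded. For lavage complications the fault is in the grade, not the capture.
- *Drug harms are recorded in none of the 192 patients.* Not supported. The recording rule applies to each subject who has lavage and could be read as covering any adverse event. The article states no capture of drug reactions, which is weaker than ruling it out.
- *The safety comparison between arms is uninformative.* Not supported. Several outcomes that bear on harm are compared between randomised arms.
- *The data monitoring committee would see too few serious events.* The Quality control section does not describe what safety data the committee reviews.
- *A trivial interruption counts as serious.* The rule speaks of ending the lavage, not of interrupting it.
- *The article calls antimicrobial escalation the main risk.* The Background raises it as a possibility and does not rank it.

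A second reply is that the article condenses a version 4 protocol that is not shown, and wider treatment-safety reporting may be there. This has force for the missing mention of drug reactions. It does not answer the definition, which the article states in closed form; a fuller text could widen it only by contradicting it.

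A third reply is that outcome-based criteria would flag much of an ICU cohort. That would be so without an attribution limit, which is why the fix has one.

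**Conclusion.** The concern holds in a limited form. The stated definition gives a wrong seriousness grade to non-fatal, life-threatening complications that neither cause arrest nor end the lavage. Adverse reactions to anti-infective treatment are not named as adverse events and are not among the outcomes, so the stated intention to evaluate the risks of mNGS is met only in part.

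The size cannot be computed: the article gives no rate for lavage complications or drug reactions. The mortality analysis and the sample size are unaffected.

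The conclusion rests on reading the definition as exhaustive, as it is written, and on the article alone. If the full protocol already grades by patient outcome and collects treatment reactions, the two texts need only be reconciled.

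**What to change.** 1. Define a serious adverse event by its consequence for the patient: death, threat to life, prolonged hospital stay or lasting disability. Apply this to events attributed to lavage or to anti-infective treatment, whether or not the lavage was completed. Arrest can stay as a named example. Ending the lavage can be kept as a separate procedural item.
2. Name adverse reactions to anti-infective treatment in the section. Record them in both arms to day 28, the horizon of the primary outcome, and report them by arm.
3. State that deaths and progression due to the pneumonia itself remain in the efficacy outcomes and are not reported again as serious adverse events.

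The cost is a revised definition, a short addition to the electronic case report form, a brief mention in site training, and somewhat more event forms. One limit should be acknowledged: clinicians are not blinded, so attribution may differ by arm, and the by-arm table should be read as descriptive. Randomisation, treatment and the primary analysis do not change.

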### Sample size

In this study, a randomized controlled trial design is used to evaluate the treatment effect of mNGS and traditional microbiological tests in patients with severe pneumonia. According to a previous report [9], we hypothesized the 28-day all-cause mortality of study group and control group to be 15% and 33%, respectively. We assumed that *α* = 0.05 (two-sided test) and *β* = 0.20. Eighty-five patients should be recruited in each group. Considering an attrition rate of 10%, the eligible participants in each group should be 96. Therefore, we determined that the sample size should be 95 in each group (*n* = 192 in total).

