## Method

### Study design

This study is a regional, multi-center, open, prospective, randomized controlled trial that will include patients with severe pneumonia, from four large tertiary hospitals in North China. A total of 192 participants will be enrolled and randomly assigned in a 1:1 ratio to either the study group (mNGS combined with traditional microbiological tests group) or the control group (traditional microbiological tests group) using the central randomization system. Patients will be provided anti-infective treatment based on clinical experience according to mNGS + traditional tests or traditional tests only for two groups. The NT-BALF trial will be conducted according to the principles of the Declaration of Helsinki [7]. The Institutional Review Board of Peking Union Medical College Hospital, Chinese Academy of Medical Sciences & Peking Union Medical College in Beijing, China, approved the trial protocol (version 4.0, reference number I-23PJ1316, date 15 August 2023). The flowchart of the protocol is shown in Fig. 1. The schedule of enrolment, intervention, and assessments following the Standard Protocol Items: Recommendation for Interventional Trials (SPIRIT) guidelines (Additional file 1) is presented in Fig. 2.

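### The Sample size section gives 96 and then 95 patients per group; 95 does not fit the stated total of 192

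*Protocol article*

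**What the plan says.** All the planning figures stand in one paragraph of the protocol article, under Sample size. The assumed event rates come first: "we hypothesized the 28-day all-cause mortality of study group and control group to be 15% and 33%, respectively". The test is two-sided at 0.05 with β = 0.20. Three statements of size follow:

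- Before attrition: "Eighty-five patients should be recruited in each group".
- After a 10% attrition allowance: "the eligible participants in each group should be 96".
- The conclusion, introduced as a consequence of the line before: "we determined that the sample size should be 95 in each group", with 192 in total given in brackets.

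The total is repeated in two other places. Study design says "A total of 192 participants will be enrolled and randomly assigned in a 1:1 ratio", and the Methods part of the abstract also gives 192 patients in a 1:1 ratio.

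**The concern.** Consecutive sentences give two values for the same quantity, the number to be randomised to each group, and the second is presented as following from the first. The second sentence also does not agree with itself: equal groups of 95 do not add up to 192.

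The derivation does not settle the matter at a glance, because each per-group figure has something in its favour. The value 95 is what 85 and 10% give by the usual formula, but it does not produce the stated total. The value 96 produces the total, but lies one above what 85 and 10% give.

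The per-group size is a figure against which a final report compares planned with achieved enrolment. With both values on record, a trial that stopped at 190 could be described either as having met its target or as two short. What is at stake is a clean statement of the plan, not the trial's ability to answer its question.

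**Working it through.** **Inputs** (protocol article, Sample size): mortality p₁ = 0.15 in the study group and p₂ = 0.33 in the control group; two-sided α = 0.05; power 0.80; attrition 10%. Allocation is 1:1 (Study design; Randomization and blinding).

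**Step 1: reproduce the 85.** Normal approximation for two proportions with unpooled variance:

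n = (z₀.₉₇₅ + z₀.₈₀)² × [p₁(1 − p₁) + p₂(1 − p₂)] / (p₂ − p₁)²

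= (1.960 + 0.842)² × (0.1275 + 0.2211) / 0.18²

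= 7.849 × 0.3486 / 0.0324 = 84.45, rounded up to **85**. The starting figure reproduces exactly.

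The section does not name its formula. Other common choices give nearby values: 86 with the arcsine transformation (85.50) and 88 with the pooled-variance form (87.18).

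**Step 2: apply 10% attrition to 85.**

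- Dividing by the retained fraction: 85 / 0.9 = 94.4, rounded up to **95**.
- Multiplying by 1.1: 85 × 1.1 = 93.5, rounded up to **94**.

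Neither gives 96. The value 96 would follow from 86 per group (86 / 0.9 = 95.6, rounded up to 96), but the section states 85.

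**Step 3: totals at 1:1.**

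| Per group | Total | Follows from 85 and 10%? | Matches the stated 192? |
|---|---|---|---|
| 95 | 2 × 95 = 190 | yes | no |
| 96 | 2 × 96 = 192 | one above | yes |

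**Step 4: does it matter for power?** Exact enumeration of the uncorrected chi-square test at two-sided 0.05, 15% versus 33%:

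| Analysed per group | Power |
|---|---|
| 85 | 80.0% |
| 86 | 80.3% |
| 95 | 84.0% |
| 96 | 84.4% |

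With 10% attrition, 95 randomised per group leaves 95 × 0.9 = 85.5 and 96 leaves 96 × 0.9 = 86.4. The pooled normal approximation gives 79.2% and 79.6% for these. On either method, choosing 95 or 96 moves power by less than half a percentage point. The chi-square test is used here only as a yardstick; the Sample size section names no test.

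**The case against.** The strongest reply is that nobody running this trial would be misled. The total is 192 in the abstract, in Study design and in the Sample size section itself. With 1:1 allocation that fixes 96 per group, which the sentence just before the slip also states. The number 190 appears nowhere. On this view one digit is wrong in a condensed journal article and the surrounding text corrects it. As for the step from 85 to 96, planning one patient more per group than the formula requires is not a mistake in size.

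Most of this stands. A reader might infer from the two per-group figures that the trial has no single enrolment target. The documents do not support that, because the total is the same in all three places. A reader might also infer that 96 and 192 are wrong sample sizes, or that the 80% power claim is at risk. They do not support that either: 96 is one above the strict result, errs upward, and leaves power essentially unchanged.

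What the reply does not remove is the contradiction. The concluding sentence pairs 95 per group with 192 in total, and at 1:1 both cannot be true. The sentence states a wrong number, so the condensed format does not account for it.

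**Conclusion.** The point holds as a minor correction. The per-group sample size is stated as 96 and then as 95, and the 95 contradicts the total of 192. The size of the contradiction is one patient per group, two overall. Separately, the step from 85 to 96 exceeds by one per group what 10% attrition yields, in the conservative direction and without explanation.

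The contradiction rests only on the article's own figures and on 1:1 allocation. The statement that strict inflation gives 95 assumes division by 0.9 with rounding up; multiplying by 1.1 instead gives 94, which is no closer to 96. The power figures assume the protocol's 15% and 33% and an uncorrected chi-square comparison. No estimate, test or conclusion of the trial changes.

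**What to change.** In the last sentence of the Sample size section, change the per-group figure from 95 to 96 and keep 192 in total. Add one clause saying that 85/0.9 gives 95 per group and that 96 per group are planned. If the authors have a specific reason for the extra patient, such as a starting value of 86 from another formula, they should give it; the article offers none, and a reason should not be supplied for them.

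Writing 95 per group and 190 in total would also be consistent, but it would mean changing the total in the abstract, Study design and Sample size, for no gain.

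The cost is an edit to one sentence. It adds no patients and leaves the design and analysis as they are.
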